#### Data Collection

For each country, based on sociocognitive behavioral change theories such as the theory of planned behavior [56], we will assess participants’ opinions regarding factors [57] that could influence their adoption and intention to use an e-DSI to improve autonomy and make decisions about housing [13]. Participants will be invited to complete a self-administered web-based survey with closed-ended questions. The survey questions will be based on the integrative model of behavior [58] to assess participants’ intention to use the e-DSI for future if they faced a housing decision [13]. Additionally, we will measure the psychosocial determinants of this behavioral intention [14] and explore their preferred role in decision making [59], their experience using technology [13], and sociodemographic variables (eg, age, sex, social economic status, and relationship between the older adult and the caregiver) [57,60].

#### Data Analysis

Our primary outcome variable is the behavioral intention of a participant to use the e-DSI; this will be measured on a 7-point Likert scale, ranging from 1 to 7. We will assess the psychosocial determinants of this behavioral intention and participants’ opinions regarding factors that could influence their use of an e-DSI by referring to questions in the domains of the NASSS (nonadoption, abandonment, scale-up, spread, and sustainability) framework [61]. We will compare data from people with and without experience using an e-DSI to explore how experience influences willingness to use it. Secondly, we will compare the data obtained in the three countries to identify any differences between health care systems, geography, and regulations.

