## Methods

### Overview of Study Design

The COORDINATEs (teChnology tO suppORt DecIsioN making about Aging aT homE) project is a multipronged study with four phases, each one under the leadership of team members in a different country. Our research questions will be addressed in three countries, with a diversified sample, using a mixed methods approach to provide rich insight into mobility patterns and decision making. Using an integrated knowledge translation approach, we will use iterative end-user consultation and feedback to tailor e-DSI technology to end users in Canada, Sweden, and the Netherlands.

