Canada, Sweden, and the Netherlands all are advanced economies with welfare states with aging populations. However, each country has a different health and welfare system that influences policies and services dedicated to aging at home versus in institutions [39,40]. Canada’s regime is liberal with a national health insurance system, while Sweden has a social-democratic welfare regime. The Netherlands has characteristics of both conservative and social-democratic regimes and an etatist social health insurance system. We will take into account the intra- and intercountry differences between older adults and between urban and rural environments. Data collection for each phase will be carried out simultaneously and in collaboration with all country teams. The target population and recruitment strategy will vary for the three data collection phases (see Table 1). Phase 1 will be under the leadership of Dutch team members and will assess mobility patterns and experiences of older adults with memory problems in all three countries. Phase 2 will be under the leadership of a Swedish team and will support the co-design of an e-DSI that integrates mobility patterns and experiences generated from Phase 1 and end users’ views and preferences for improving the usability and adaptability of technology [41]. Phase 3 will be under the leadership of Canadian team members who will oversee web surveys—one in each country—on the end users’ intention to use personalized e-DSIs to improve autonomy and inform housing decisions. Lastly, for Phase 4, the leadership in all three countries will triangulate and compare results to develop an action plan for scaling up e-DSI development to improve autonomy among older adults with memory problems who live at home and inform their SDM processes about housing options. Informed by the Good Reporting of A Mixed Methods Study (GRAMMS) reporting guidelines [42], and applying an integrated knowledge translation approach [43], we will explore synergies between the data, inform the design of the sequential phases, and link the findings.

**Table 1 table1:** Target population and recruitment strategy: Phases 1 to 3.

Project phase	Target population	Recruitment strategy
Phase 1	Older adults with self-reported memory problems who live at home	Referrals from nurses and physicians Referrals from home health care teams Self-referrals from flyers in public spaces Self-referrals from media

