#### Data Analysis

In line with other studies using similar methods, the sample size of 20 participating older adults per country is based on the expectation that it should reach data saturation (eg, [28,48,49]). A database that includes quantitative data from travel diaries will be created in Microsoft Access 2016, and the data will be cleaned, analyzed descriptively, and linked to the GPS data based on unique identifiers. All data, aside from the GPS data, will be anonymized and pseudonymized. The GPS data are extremely privacy-sensitive as they provide location information, so they will be securely stored in a virtual research workspace (VRW) created by the Center for Information Technology at the University of Groningen. Only project staff can access this environment via two-factor authentication (ie, password and text message). When analyzing the GPS data, we will work with the real location data within the VRW. The real locations are needed as the location and movement data need to be connected to other layers of information, such as roads, shops, and health care services. GPS data will be analyzed using the geographic information system programs V-Analytics and ArcMap 10.5.1 (Esri) to create maps with visited places and trajectories, including speed, duration, and length of time on an activity. The qualitative data generated through the walking interviews and debrief interviews will be transcribed verbatim, open contentcoded using a grounded theory method [50], and analyzed thematically using the software package ATLAS.ti 8.4 (Scientific Software Development GmbH). All data sources will be compared and combined to check for incongruences between the data sources to obtain a comprehensive overview of the participants’ mobility in association with their respective environments. Furthermore, we will summarize the themes from the in-depth interviews, translate them into English, triangulate data from the three countries, and further compare differences between health care systems, geography, and regulations.

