### Phase 4: Inform Future SDM Processes

For the final phase of the project, we will synthesize, triangulate, and compare data from all project phases and collaboratively explore privacy issues. Validation and interpretation of data will be accomplished with consensus meetings between researchers and end users [62]. Data from the three countries—Canada, Sweden, and the Netherlands—will be triangulated and compared to assess differences in contextual factors (ie, health care system, policy, geography, and culture), and we will make recommendations for technology implementation to improve autonomy and inform SDM about housing in the three countries. At the end of Phase 4, end users in each country will participate in a workshop where project results will be presented and discussed. As an output, we will acquire knowledge about differences and similarities in mobility patterns and experiences with using GPS and an e-DSI among older adults with memory problems and their caregivers, their respective assessments of its contribution to improving autonomy and emerging housing decisions, their willingness to continue using it, and factors that influence usage. After evaluating the impact of an e-DSI for continuing to age at home and for ongoing housing decisions among older adults and their caregivers, we will propose country-specific action plans to scale up e-DSIs and evaluate their implementation by home care services. We will explore opportunities to continue the consortium and form an infrastructure for continuous collaboration between the three countries.

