Finally, new technologies such as GPS tracking can infringe on people’s privacy, an issue that is highly relevant today. For example, more people are using apps that provide contact tracing for people infected with COVID-19. In our cross-country comparisons, we will investigate the ethical issues involved in working with tracking technologies with older adults in the three countries. There is little research on the ethical implications of these technologies with older adults and their caregivers [63-65]. Notably missing are discussions about translating general ethics and privacy principles into concrete guidelines in different national settings. Therefore, in accordance with guidance from our four ethics boards, we will advance the current state of the art in this domain by developing country-specific ethical guidelines for practice. There are some anticipated challenges and limitations of this research project. Although most of the data collection in each phase will take place in the language of each country, with Canada having two official languages, the overarching research process will be undertaken in English, and this may affect the capacity of team members, including older adults and caregivers, to fully participate. Communicating among different countries and time zones can be a challenge. Therefore, it is critical for this international team to have established solid lines of communication and formal institutional consortium agreements to ensure the success of the project. Second, despite the increasing computer literacy levels among older adults [66,67], some, especially those who are socioeconomically disadvantaged, do not have access to a computer with internet access and therefore will not be eligible to participate in Phase 2 of this project.

This protocol outlines an original approach to integrating mobility patterns and mobility experiences of older adults with memory problems into an e-DSI to improve their autonomy and ultimately inform SDM about housing options. The results will contribute to the development of technology that supports older adults’ autonomy and housing decisions in general. Furthermore, the international collaboration with end users can provide valuable insights into the intention to use technology for housing decisions and barriers to its use.

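### Phase 3 country differences cannot be attributed to health care system or national regulations, because each country is the only example of its system and has its own survey firm

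*Protocol article*

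**What the plan says.** The Protocol article, Phase 3, Data Analysis, names behavioral intention on a 1-to-7 scale as the primary outcome. It plans a comparison by e-DSI experience, and then the country comparison: "Secondly, we will compare the data obtained in the three countries to identify any differences between health care systems, geography, and regulations".

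The Overview of Study Design explains why these countries were chosen. It says that "each country has a different health and welfare system that influences policies and services" and assigns one regime to each: "Canada’s regime is liberal with a national health insurance system, while Sweden has a social-democratic welfare regime", and "The Netherlands has characteristics of both conservative and social-democratic regimes and an etatist social health insurance system". No two countries share a system. The same section says that differences within and between countries, and between urban and rural settings, will be taken into account. It gives no method for this.

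Phase 3, Participants, has a separate survey firm in each country recruiting 70 older adults and/or caregivers from its panel, with senior and caregiver associations as a further route. Phase 3, Data Collection, gives age, sex, socioeconomic status and the caregiver relationship as examples of sociodemographic variables, and also covers experience with technology.

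Similar wording appears for the Phase 1 interview themes ("further compare differences between health care systems, geography, and regulations") and for the Phase 4 synthesis ("compared to assess differences in contextual factors (ie, health care system, policy, geography, and culture"). The limitations in the Discussion cover working language, communication across countries and access to computers. They do not cover this point.

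**The concern.** The sentence in Phase 3 names the factors that the country comparison is meant to reveal. The data come from a closed-ended survey, so whatever Phase 3 itself says about those factors must come from contrasts between three country samples. With one country per system, a contrast between two countries is at once a contrast of system, of national regulations, of survey firm and panel, and of everything else that is fixed by country.

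Suppose mean intention is lower in one country. That could reflect its health care system. It could equally reflect a panel with a different share of caregivers, since the plan fixes no mix of older adults and caregivers per country. If the result is written up in the terms of the Phase 3 sentence, a panel difference could be presented as a system or regulation difference. It could then enter the Phase 4 recommendations on implementing the technology in each country.

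**Working it through.** The plan gives no figure for the country comparison, so there is none to reproduce beyond the total: 3 × 70 = 210, which agrees with Phase 3, Participants. The sample size there is set for a mean within each country, not for differences between countries. Nothing below depends on it.

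**Inputs**
- Countries: 3 (Overview of Study Design).
- Systems: 3, one per country (same section).
- Survey firms: one per country (Phase 3, Participants).
- Respondents: n = 70 per country.

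**Step 1: what a country contrast estimates.** Write the expected intention score in country j as

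μ_j = μ + s_j + r_j + f_j,

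with s for system, r for national regulations and f for survey firm and panel. For two countries A and B,

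μ_A − μ_B = (s_A − s_B) + (r_A − r_B) + (f_A − f_B).

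The data estimate the left side only. Any split of that total among the three brackets fits equally well.

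**Step 2: rank of the design matrix (210 rows).**
- Intercept plus two country indicators: 3 columns, rank 3, so 2 degrees of freedom between countries.
- Intercept plus system and regulations, two indicators each: 1 + 2 × 2 = 5 columns. The indicators repeat the country columns, so the rank stays at 3.
- Intercept plus five factors fixed by country (system, regulations, policy, culture, national geography): 1 + 5 × 2 = 11 columns, rank 3.

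The two national factors named in the Phase 3 sentence, system and regulations, are already inseparable. The result does not need policy and culture, which are named only in Phase 4.

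**Step 3: does a larger sample help?** No. The standard error of a difference between two countries is SD × √(2/n), which shrinks as n grows. The rank does not depend on n. A larger survey measures the same mixed total more precisely.

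**Step 4: geography.** Adding one urban/rural indicator that varies within country raises the rank from 3 to 4. Adding its interaction with country raises it to 6. That part of geography is estimable if the variable is recorded. National geography remains tied to country.

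**Step 5: covariate adjustment.** Age, sex and respondent type vary within country, so they can be adjusted for. This removes differences in sample composition on those variables. It does not separate system from regulations, or either of them from unmeasured features of the panel.

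**The case against.** The strongest defence is that the article claims little. It states no test or causal estimate of a system effect, the country comparison comes second, and the sample size is set within country. Since each country is described as a different system, the sentence may be no more than a loose way of saying that three country contexts will be compared. The study is mixed-methods, and Phase 4 interprets results through triangulation and meetings with end users, where participants can say how a service or rule affected them.

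Much of this stands, and it limits the point to the Phase 3 survey. It does not remove the point. The sentence does name the factors to be identified, a closed-ended survey cannot identify them, and no stated limitation says so.

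Several stronger readings are tempting but not supported:

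- *That geography is aliased as fully as system and regulations.* The Overview of Study Design foresees urban/rural and within-country differences. The Phase 3 variable list is given as examples, so the absence of an urban/rural item there does not show that the questionnaire lacks one.
- *That Phases 1 and 4 fail for the same reason.* They rest on interview themes and triangulation, so attribution there need not depend on three country means, and the degrees-of-freedom argument does not carry over directly.
- *That the plan compares unadjusted samples.* The article specifies neither an adjusted nor an unadjusted model. Adjustment is a recommendation here, not the correction of a stated error.
- *That power at 70 versus 70 measures the problem.* The chance that an assumed gap reaches significance is the same in any two-sample comparison of that size and says nothing about aliasing.
- *That Canada offers an internal yardstick for differences not due to system, "with Canada having two official languages" and two Canadian ethics boards.* The Phase 3 recruitment plan describes a survey firm in each country and no survey sites or language strata.

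**Conclusion.** The point holds for Phase 3. The survey can describe differences in intention between the three country samples. It cannot attribute them to health care system or to national regulations, nor separate either from survey firm and panel. There are 2 degrees of freedom between countries, and every factor fixed by country uses the same 2, at any number of respondents. The size of the problem is therefore structural and not a matter of precision.

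This rests on two statements in the article: that each country has a different system, and that each has its own survey firm. It also takes national regulations to be constant within country. It needs no assumption about the SD or the size of any difference.

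The surveys remain usable; only the stated inference needs correcting. A reader might go further and infer that panel differences will be reported as system effects. The documents show only that the wording leaves room for this. The action plans for each country can rest on what respondents there report, without an attributed cause. The change should be made because it is cheap and alters what the study may conclude.

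**What to change.** 1. In Phase 3, Data Analysis, reword the last sentence so that the aim is to compare the three country samples. Treat health care system and regulations as hypotheses, to be interpreted with the qualitative material from Phases 1, 2 and 4.
2. Add to the limitations in the Discussion that, in Phase 3, system, national regulations and survey firm are confounded with country. Carry the same statement into the Phase 4 synthesis.
3. Report Phase 3 country contrasts both unadjusted and adjusted for respondent type (older adult or caregiver), age and sex. The survey already collects these or can identify them.
4. Adjust for socioeconomic status and technology experience only in a sensitivity analysis. Both may lie on the pathway from country context to intention, and adjusting for them could remove part of what the comparison is meant to show.
5. If urban/rural residence is not already in the Phase 3 questionnaire, add it, and address geography by contrasts within country.

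The cost is a few sentences, one adjusted model with a sensitivity version, and at most one questionnaire item. The downside is a less ambitious statement about health systems.

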### Phase 4: Inform Future SDM Processes

For the final phase of the project, we will synthesize, triangulate, and compare data from all project phases and collaboratively explore privacy issues. Validation and interpretation of data will be accomplished with consensus meetings between researchers and end users [62]. Data from the three countries—Canada, Sweden, and the Netherlands—will be triangulated and compared to assess differences in contextual factors (ie, health care system, policy, geography, and culture), and we will make recommendations for technology implementation to improve autonomy and inform SDM about housing in the three countries. At the end of Phase 4, end users in each country will participate in a workshop where project results will be presented and discussed. As an output, we will acquire knowledge about differences and similarities in mobility patterns and experiences with using GPS and an e-DSI among older adults with memory problems and their caregivers, their respective assessments of its contribution to improving autonomy and emerging housing decisions, their willingness to continue using it, and factors that influence usage. After evaluating the impact of an e-DSI for continuing to age at home and for ongoing housing decisions among older adults and their caregivers, we will propose country-specific action plans to scale up e-DSIs and evaluate their implementation by home care services. We will explore opportunities to continue the consortium and form an infrastructure for continuous collaboration between the three countries.

### Ethical Considerations and Trial Registration

A review for issues regarding human subjects has been obtained from four research ethics committees. Ethics approval has been obtained by the Research Ethics Committee, Faculty of Spatial Sciences, University of Groningen; Centre intégré universitaire de santé et de services sociaux de la Capitale-Nationale, L'Université Laval; the Swedish Ethical Review Authority; and the Health Research Ethics Board, University of Alberta. For all phases of data collection, participants will be asked to sign an informed consent form. Where appropriate, we will ask informal caregivers to sign a consent form. This trial was registered at ClinicalTrials.gov (NCT04267484).

## Results

The study opened for recruitment in the Netherlands in November 2018 and in Canada and Sweden in December 2019. Data collection will be completed by April 2021. Given the COVID-19 pandemic and the different lockdown approaches taken by each country, data collection may be adapted using virtual methods.

## Discussion

We have described the methods for exploring how adding data about personal mobility patterns of older adults to an e-DSI has the potential to improve their autonomy and inform future SDM processes about housing options. Participants included older adults living at home with memory problems and their caregivers as well as a diverse group of stakeholders. This study will contribute to the mobility literature on older adults with memory problems and inform the development of technology that augments self-management among older adults affected by memory loss, their caregivers, health care professionals, and policy makers [13,14,16,30,60].

The proposed study is a highly original approach to the potential of technology use with older people with memory problems. First, this is an interdisciplinary, interprofessional, intersectorial, and international study. This question is often addressed in isolated contexts without the mutually enriching possibilities of working together with other disciplines, professions, technological traditions, and cultures. Second, while personalized medical care such as gene testing or drug treatment selection is becoming the norm in specific contexts, personalized data have rarely been used to empower older people with memory loss. The results not only have the potential to keep older people safely at home for longer but will provide deep insights into their physical and emotional relationship with their surroundings and the consequences of displacing them into a new environment. Third, one of the persistent problems we have seen with decision making about housing among older adults is that their autonomy or mobility needs change from day to day. Thus, the information needed for decision making also changes from day to day. This technology could relieve the deep distress experienced by older people and their families facing this decision by providing reliable and relevant ongoing data that indicate the individual’s changing needs for on-the-spot decision making.

Finally, new technologies such as GPS tracking can infringe on people’s privacy, an issue that is highly relevant today. For example, more people are using apps that provide contact tracing for people infected with COVID-19. In our cross-country comparisons, we will investigate the ethical issues involved in working with tracking technologies with older adults in the three countries. There is little research on the ethical implications of these technologies with older adults and their caregivers [63-65]. Notably missing are discussions about translating general ethics and privacy principles into concrete guidelines in different national settings. Therefore, in accordance with guidance from our four ethics boards, we will advance the current state of the art in this domain by developing country-specific ethical guidelines for practice. There are some anticipated challenges and limitations of this research project. Although most of the data collection in each phase will take place in the language of each country, with Canada having two official languages, the overarching research process will be undertaken in English, and this may affect the capacity of team members, including older adults and caregivers, to fully participate. Communicating among different countries and time zones can be a challenge. Therefore, it is critical for this international team to have established solid lines of communication and formal institutional consortium agreements to ensure the success of the project. Second, despite the increasing computer literacy levels among older adults [66,67], some, especially those who are socioeconomically disadvantaged, do not have access to a computer with internet access and therefore will not be eligible to participate in Phase 2 of this project.

This protocol outlines an original approach to integrating mobility patterns and mobility experiences of older adults with memory problems into an e-DSI to improve their autonomy and ultimately inform SDM about housing options. The results will contribute to the development of technology that supports older adults’ autonomy and housing decisions in general. Furthermore, the international collaboration with end users can provide valuable insights into the intention to use technology for housing decisions and barriers to its use.

